### Trial procedure and timeline

Figure 1 and Table 1 provide an overview of the trial flow and assessment schedule, respectively. The study duration is 15 months, which includes 3 months of the intervention period (active phase) for the participants. The last follow-up visit will take place 12 months after the intervention. Assessments will be conducted at the Department of Cardiology and Vascular Medicine, West German Heart and Vascular Center, University Hospital Essen, Germany.

Interested patients will be screened for eligibility and receive further information about the study conditions, data storage, and data safety (oral and written). The study team at the respective clinic will conduct a baseline diagnostic assessment to determine eligibility. If the patient meets the inclusion criteria and does not have any exclusion criteria and provides written informed consent, they will be included in the study.

After completing the baseline assessment, the patient will be randomly assigned to either the intervention group or control group. Patients will be notified of their group allocation and will receive information on how to access the intervention (intervention group). Participants allocated to the control group will receive information about the further steps (assessment schedule). At the end of the 3-month experimental or control intervention period, patients will complete a post-treatment diagnostic assessment and four follow-up diagnostic assessments at one, 3, 6, and 12 months after the intervention.

If a patient drops out during the intervention (i.e., no login for 4 weeks), they will receive an e-mail containing a link to a short questionnaire that assesses their reasons for dropping out.

### Sample size calculation

The sample size calculation was performed using the R-package “Superpower” [53]. The primary hypothesis is that the intervention is superior in terms of reducing stress compared to standard care (control group) at T1. To assess the efficacy of the intervention, an ANCOVA with the primary outcome variable at T1 as the criterion, the group variable (intervention vs. control group) as a between-subject factor, and the individual baseline levels at T0 as a covariate will be performed. A subsequent mixed ANOVA with the respective measurements (T0–T5) as a within-subject factor and the group variable (intervention vs. control group) as a between-subject factor will then serve to explore the intervention’s effect at follow-up. For the sample size calculation, a preferred test power of 1-ß = 0.80 was chosen. We assume a moderate effect size of *d* = 0.5 for the baseline-adjusted comparison between the intervention and control group at T1. Furthermore, and based on previous studies [54], we expected the correlation between repeated measures to be *r* = 0.5. According to the power analyses, an effective sample size of *n* = 98 (i.e., 49 participants per group) would yield a statistical power of 80.34 for the above mentioned ANCOVA analysis. With the same amount of participants, we reach a power of 95.8 for the above-mentioned mixed ANOVA (given a rather conservative assumption of the sole difference between the intervention and control group to occur at T1). Based on existing literature regarding eHealth trials [55], we assume a dropout rate of 30%. Based on the preliminary work related to this study protocol [31, 32] and recommended measures to increase usability, especially user experience [55], a dropout rate in the lower level was assumed. Consequently, 128 participants (64 per group) are needed.

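### The 95.8% power stated for the mixed ANOVA does not follow from 49 per group: the plan's own inputs give about 68%

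*Protocol article*

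**What the plan says.** The Sample size calculation section of the protocol article plans an ANCOVA at T1 as the primary test, followed by "A subsequent mixed ANOVA with the respective measurements (T0–T5) as a within-subject factor" and group as the between-subject factor. The inputs are given in one place:

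- Effect: "We assume a moderate effect size of *d* = 0.5 for the baseline-adjusted comparison between the intervention and control group at T1".
- Correlation: "we expected the correlation between repeated measures to be *r* = 0.5".
- Target: "a preferred test power of 1-ß = 0.80 was chosen".
- Size: 98 participants in total, "49 participants per group", for a stated ANCOVA power of 80.34%.

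The section then adds: "With the same amount of participants, we reach a power of 95.8 for the above-mentioned mixed ANOVA", with the pattern of means described as "given a rather conservative assumption of the sole difference between the intervention and control group to occur at T1". The total is finally raised to 128 (64 per group) for an assumed 30% dropout.

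The Statistical methods section uses the mixed ANOVA to judge whether the effect is maintained at follow-up. The Objectives section lists stress at T2 to T5 among the secondary hypotheses.

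**The concern.** The two power figures sit oddly together. The ANCOVA tests the T1 difference with one degree of freedom and adjusts for baseline. The mixed ANOVA tests the same single difference spread over a five-degree-of-freedom interaction. If the groups differ at T1 only, the second test should not be far more powerful than the first at the same sample size, yet the article gives 95.8% against 80.34%.

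What is at stake is how a non-significant interaction will be read. At 95.8% power, it would look like strong evidence that the groups do not differ over time. At about 68%, it would be missed about one time in three even if the assumed effect were real.

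**Working it through.** **Inputs.** From the Sample size calculation section: n = 49 per group, d = 0.5 at T1 and zero at T0 and T2–T5, r = 0.5 and six occasions. Three things are assumed: SD = 1 at each occasion, equal correlation between all pairs of occasions, and alpha = 0.05, which the article does not state.

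**Step 1: reproduce the ANCOVA figure.** With d on the raw SD, the residual variance after baseline adjustment is 1 − 0.5² = 0.75.

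- Noncentrality = (49/2) × 0.25 / 0.75 = 8.17 on 1 and 95 df.
- Power = 80.8% with the covariate treated as fixed, and 80.3% with it treated as random. The article states 80.34%.
- If d = 0.5 were instead on the baseline-adjusted scale, power would be 68.8%, which does not match.

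This confirms the reading of n, d, r and alpha.

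**Step 2: the mixed ANOVA at the same size.** For the group-by-time interaction:

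λ = (n/2) × Σ(d_j − d̄)² / (1 − r), df1 = 5, df2 = 5(2n − 2)

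With d = (0, 0.5, 0, 0, 0, 0), the mean is 0.5/6 and Σ(d_j − d̄)² = 0.25 × 5/6 = 0.2083.

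| n per group | λ | df | Power |
|---|---|---|---|
| 45 (128 × 0.7 ≈ 90 in total) | 9.38 | 5, 440 | 63.8% |
| **49 (the plan)** | **24.5 × 0.2083 / 0.5 = 10.21** | **5, 480** | **68.2%** |
| 64 (all randomised) | 13.33 | 5, 630 | 81.4% |
| 98 | 20.42 | 5, 970 | 95.5% |

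A simulation of 20,000 trials gave 68.4% at 49 per group and 95.5% at 98 per group.

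**Step 3: can another reading give 95.8% at 49 per group?**

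- Alpha 0.01, 0.025 or 0.10: 44%, 58% or 79%.
- Multivariate test of the interaction: 65.7%.
- T0 and T1 only: 68.8%. T1–T5 only: 70.0%.
- Group main effect: 8.3%. Time main effect with a flat control group: 68.2%, because it has the same noncentrality.
- d = 0.577 (0.5 rescaled for baseline adjustment): 82.1%.
- Generic f = 0.25 with six measures: above 99.9%.
- r = 0.75 or d = 0.71: about 95.4%, but the plan states 0.5 for both.

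Within the stated inputs, only 98 per group comes close to 95.8%.

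**Step 4: is the T1-only pattern conservative?** Not for the question the model is meant to answer. A difference of 0.5 held from T1 through T5 gives the same Σ(d_j − d̄)², again 5/6 × 0.25, and so 68.2%. A fading effect (0.5, 0.4, 0.3, 0.2, 0.1) gives 59.3%. Patterns that persist for part of follow-up do better: 89.3% for two visits and 92.9% for three. Even the best of these stays below 95.8%.

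**The case against.** The strongest objection concerns weight. The sample size comes from the ANCOVA; the 95.8% figure is added afterwards and drives neither the total, the primary test nor any decision rule. The article also says that the mixed ANOVA explores the follow-up effect, and it sets the 80% target for a calculation that rests on the ANCOVA. All of this stands, and it limits the consequence to a secondary analysis.

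A second objection is that, with a difference at T1 only, neither 95.8% nor 68% is power to detect an effect at T2–T5. That is correct for the pattern as written. It does not make the figure harmless, because a fully maintained effect of 0.5 also gives 68.2%.

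Three narrower points call for care in wording:

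- Alpha is an assumption, although no value from 0.01 to 0.10 rescues the figure.
- The explanation that 98 was entered per group is an inference, since the code is not shown.
- The time main effect could reach about 95% if the control group also shifted by 0.10 SD at T1. The article states no such shift, and the time effect does not compare the groups. Still, it would be too strong to say that no effect in the model could ever reach the stated power.

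**Conclusion.** The concern holds. The stated 95.8% is wrong for 49 per group. Under the plan's own inputs the interaction has about 68% power, some 28 points lower, and the type II error is about 32% rather than about 4%. If 30% of the 128 are lost, power is about 64%; it passes 80% only if all 64 per group are analysed (81.4%).

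This rests on equal correlations of 0.5 and an alpha of 0.05, and reproducing the ANCOVA power supports both r = 0.5 and that alpha. The mismatch is a matter of arithmetic; its cause is only likely. The primary analysis and the planned total of 128 are not affected by this point.

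**What to change.** In the Sample size calculation section:

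- Rerun the mixed ANOVA power with 49 as the per-group size, and state the alpha used.
- Replace 95.8 with about 68% for 98 analysed participants, and add that it is about 64% for 90.
- Drop the description of the T1-only pattern as conservative, since a fully maintained effect gives the same power and a fading one gives less.
- Describe the follow-up analysis as supportive, and report the group differences at T2–T5 with confidence intervals, so that a non-significant interaction is not read as absence of effect.

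The cost is one corrected figure and one or two sentences. The stated power becomes less favourable. No extra patients and no change to the primary analysis are needed.

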**Methods and analysis:**

This randomized controlled confirmatory interventional trial with two parallel arms has assessments at six measurement time points: baseline (T0, prior randomization), post-treatment (T1), and four follow-ups at months 1, 3, 6, and 12 after intervention (T2, T3, T4, and T5). We will include patients with confirmed diagnosis of IHD, high-perceived stress, and use of an internet-enabled smartphone. Patients will be randomized into two groups (intervention vs. control). The proposed sample size calculation allocates 128 participants in total. The primary analysis will be performed in the intention-to-treat population, with missing data imputed. An ANCOVA with the outcome at T1, a between-subject factor (intervention vs. control), and the participants’ pre-intervention baseline values as a covariate will be used. Different ANOVAs, regression, and descriptive approaches will be performed for secondary analyses.

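### The 30% dropout allowance was added to 98 instead of divided out, so 128 randomised leaves about 90 with T1 data and about 77% power, not 80%

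*Protocol article*

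**What the plan says.** The Sample size calculation section sets the target: "a preferred test power of 1-ß = 0.80 was chosen". Its design inputs are "We assume a moderate effect size of *d* = 0.5 for the baseline-adjusted comparison" and "we expected the correlation between repeated measures to be *r* = 0.5". From these it derives "an effective sample size of *n* = 98 (i.e., 49 participants per group"), which "would yield a statistical power of 80.34 for the above mentioned ANCOVA analysis".

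It then turns to attrition. Citing the eHealth literature, it says "we assume a dropout rate of 30" per cent, and adds that preliminary work and usability measures justify a rate at the low end. It closes with "Consequently, 128 participants (64 per group) are needed".

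The abstract repeats the total: "The proposed sample size calculation allocates 128 participants in total".

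**The concern.** The section calls 98 the effective sample size, meaning what should be left after dropout. For 98 to be left when 30% are lost, 98 must be 70% of the number randomised. The printed 128 does not meet that condition. It looks like 98 plus 30% of 98, a common shortcut that applies the dropout rate to the wrong base.

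The group size of 49 was chosen to sit just above 80% power, so nothing is in reserve to absorb the error. If dropout is as assumed, the confirmatory comparison at T1 runs below the power the plan chose, and readers of the protocol will believe otherwise.

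**Working it through.** **Inputs, all from the Sample size calculation section unless noted**

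- Effect at T1: d = 0.5
- Correlation between repeated measures: r = 0.5
- Effective sample: 98, 49 per group
- Stated ANCOVA power: 80.34%
- Dropout: 30%
- Randomised: 128, 64 per group, allocated 1:1 (Randomization and blinding section)
- Significance level: not stated in the article; two-sided 5% is assumed here

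**Step 1. Reproduce the plan's power at 98.**

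With one baseline covariate, the ANCOVA residual SD is √(1 − r²) = √0.75 = 0.866 of the raw SD. The adjusted standardised effect is 0.5 / 0.866 = 0.577. For n per group, the noncentrality is 0.577 × √(n/2), with 2n − 3 degrees of freedom.

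At n = 49 this is 0.577 × √24.5 = 2.86 on 95 df, which gives 80.8% when the baseline is treated as fixed. Treating the baseline as random, by averaging over its chance imbalance between groups, gives 80.34%. That is the printed figure to two decimals, so the model and the assumed 5% two-sided level can be taken as the sponsor's. (In the fixed-covariate version, a one-sided 5% test would give 88.4%.)

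**Step 2. Reproduce the 128.**

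- Total: 98 × 1.3 = 127.4, rounded up to 128
- Per group: 49 × 1.3 = 63.7, rounded up to 64

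Both printed figures match this multiplication.

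**Step 3. Apply 30% dropout to those randomised.**

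- What 128 leaves: 128 × 0.70 = 89.6, or 64 × 0.70 = 44.8 per group
- What 98 requires: 98 / 0.70 = 140, or 70 per group
- Dropout that 128 can absorb: 1 − 98/128 = 30/128 = 23.4%

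**Step 4. Power at what remains.**

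| Per group with T1 data | Baseline random | Baseline fixed |
|---|---|---|
| 49 | 80.3% | 80.8% |
| 48 | 79.5% | 79.9% |
| 45 | 76.8% | 77.3% |
| 44 | 75.9% | 76.3% |

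The smallest group size that reaches 80% is 49 under either version. The loss at 45 per group is 80.3 − 76.8 = 3.5 points.

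**The case against.** **Dropout is not the same as a missing T1 outcome.** This is the strongest objection. The article defines dropout as four weeks without a login. A patient who stops using the app can still attend T1 at the clinic, and Table 1 schedules the combined stress measure in its dropout column. Control patients have no app and cannot meet the definition. If 30% were lost from the intervention arm only, 45 + 64 = 109 would remain and power would be 83% to 84%. The loss of power is therefore conditional on 30% missing T1 outcomes in both arms. But the sample size section uses the 30% in exactly that way: it inflates both arms equally and treats 98 as what is left. The step has to follow its own premise.

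**The primary analysis is intention-to-treat with multiple imputation, so all 128 enter the ANCOVA.** This is right as to wording: the 90 are participants with observed T1 data, not the analysis set. It does not rescue the power. The predictors named under Statistical methods are sex, age and baseline values, which carry little information about T1 beyond what the ANCOVA already uses. If imputation did restore the loss, no inflation would have been needed.

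**The section says a rate at the low end was assumed, which might mean less than 30%.** No lower figure is given, and the 23.4% that would justify 128 appears nowhere. The sentence reads more naturally as the reason for choosing 30% over something higher, and the exact match to × 1.3 points the same way.

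**The effect is small.** It is: no estimate, error rate or analysis population changes.

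**Conclusion.** The point holds. An effective sample of 98, 30% dropout and 128 randomised are inconsistent, and 128 is explained exactly by multiplying by 1.3. Under the plan's own premises, about 90 participants would have observed T1 data instead of 98. Power for the primary ANCOVA would be about 77% instead of 80.34%. The gap in randomised participants is 140 − 128 = 12.

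This rests on three assumptions: a two-sided 5% test, which the exact reproduction of 80.34% supports; 30% missing T1 outcomes in both arms, as the section's own inflation implies; and little recovery of information through imputation. It also takes d = 0.5 as a difference in raw SD units, the only reading that yields the printed power. If d were already on the baseline-adjusted scale, 49 per group would give only about 69%, and the shortfall would be larger.

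The size is modest and the validity of the trial is untouched, but the figure is wrong as written and concerns the single confirmatory test.

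**What to change.** Correct the closing sentence of the Sample size calculation section. Any one of these is consistent:

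- Keep 128 and 30% dropout, and state that about 90 participants are expected to have T1 data, with power of about 77%.
- Keep 128 and 80% power, and state that this holds only if no more than 23% of T1 outcomes are missing. Support that rate.
- Keep 80% power and 30% dropout, and randomise 140 (70 per group).

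In the same place, state the significance level and sidedness, and say that dropout here means a missing T1 outcome and not a lapse in logins. If the total changes, change it in the abstract too.

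The first two options cost one sentence and a slightly less favourable power statement. The third costs 12 more participants.

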### Randomization and blinding

Balanced block randomization (1:1 randomization) will be applied, using a standard computer algorithm. No stratification will be applied. It is assumed that the randomization process will result in a balance of the prognostic factors. The study personnel will communicate the result of the allocation to the participants after enrollment and randomization process.

The blinding process will include almost all stakeholders within the treatment process. Treating physicians, just like assessors and statisticians (primary analysis) will be blinded to group allocation to ensure objective analyses. Only blinding for patients will be performed due to the knowledge of each individual about the treatment with or without an app. Demasking for physicians, assessors, or statisticians is not planned.

### Data management, data storage, and dissemination policy

To ensure participant confidentiality, their data will be pseudonymized. All standard operating procedures will adhere to legal requirements, as outlined in the data management plan. Both the study team and the patients themselves will enter data electronically. Paper-based data will be transferred to the electronic database. Following Good Clinical Practice guidelines, important trial data (including signed informed consent forms, patient identification lists, and original clinical findings) will be archived for 10 years after the trial’s completion or termination. Patient documents will be stored in line with hospital regulations. Stored data during and after the trial will only be accessible to authorized staff.

We will adhere to Good Clinical Practice guidelines and follow the data-sharing statements outlined in The New England Journal of Medicine [56, 57]. Once the major results of the trial are published, the collected data will be available upon reasonable request in an anonymous format. In addition, we will store and make available the statistical analysis plan and other relevant documents upon request. Access to the data storage will be limited to authorized personnel only. Patient consent forms will include a section covering the aforementioned aspects of data storage and sharing.

Our approach to disseminating the trial’s progress and outcomes will include several measures. First, we will establish a project homepage that will provide regular updates to the public about the trial’s development, opportunities for participation (such as workshops and conferences), and significant findings. This website will remain active even after the recruitment is closed, serving as a central point of access for future research and results dissemination. We will also publish the main trial results open-access in a peer-reviewed journal and make them publicly available in the clinical trial registry. Additionally, we will present the findings at conferences and communicate scientific results in lay language through press releases, social media, and patient forums. To ensure the results reach the affected population and the public, we will collaborate with patient representatives and patient organizations to develop targeted, patient-oriented information campaigns.

### Statistical methods

The primary goal of this trial is to assess the efficacy of the intervention compared to the control group in terms of reducing stress directly after the intervention. For this purpose, an analysis of covariance (ANCOVA) with the outcome at T1, a between-subject factor (intervention group vs. control group), as well as the participants’ pre-intervention baseline values (T0) as a covariate will be used. The primary analysis will be performed in the intention-to-treat population, with missing data imputed in the case of dropout. Imputation will be calculated using the SPSS multiple imputation module with “monotone missing pattern” (as we will use complete data for sex, age, and baseline data of primary and secondary outcomes). The number of imputations will be set to 3000, and the seed will be set to the date of the analysis (ddmmyy). Interim analyses are not planned.

Subsequent mixed ANOVAs with a between-subject factor coding the group membership (intervention vs. control group) and a within-subject factor for the respective measurement (T0-T5) will serve to assess if the effect of the intervention is maintained at follow-up. Further clinical endpoints will be analyzed in a similar fashion. If, in any of the above-mentioned analyses, we find severe violations of normality or homoscedasticity, robust procedures (e.g., robust regression analyses, generalized estimating equations, or robust mixed linear models) will be used, instead. In case of violation of the sphericity assumption in the mixed ANOVA, appropriate corrections will be used (Huynh-Fieldt or Greenhouse–Geisser).

Treatment satisfaction, usability, and usage behavior will be analyzed descriptively. Furthermore, *t*-tests (or, in the case of a violation of the normality assumption, the Mann–Whitney *U*-test) and, for categorical variables, *χ*
^2^ tests (or, for variables with small cell sizes, Fisher’s exact tests) will be used to account for unlikely but possible differences in demographic and baseline parameters between the two groups. In addition, different groups (e.g., dropouts; group completing the intervention; group benefiting from the intervention) will be analyzed using analyses of variance and *χ*
^2^ tests to determine whether they differ from each other in terms of sociodemographic and clinical data.

Furthermore, exploratory analyses including usage behavior and clinical outcome parameters (all assessments, including in-treatment assessments) will be conducted using, for example, different types of regression analyses. Time to dropout will be examined as a secondary endpoint, utilizing both the Kaplan–Meier estimate and the Cox proportional hazards regression.

Additionally, separate tabulations and line listings of adverse events and severe adverse events will be generated to thoroughly analyze safety.

To evaluate the cost-effectiveness of the intervention, the incremental cost-effectiveness ratio (ICER) and incremental cost-utility ratio (ICUR) will be calculated as the ratio of the mean cost difference and the mean difference in health effects (measured in terms of either stress (primary outcome) or QALY) between study groups during the follow-up period. The analysis will also consider the uncertainty of results.

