### Objectives, hypotheses, and other study goals

*The objective* of the “mStress-IHD” trial is to assess the efficacy and cost-effectiveness of the mHealth intervention “mindfulHeart” compared to standard care (control group) in terms of reducing stress in patients with ischemic heart disease (IHD).

*Primary hypothesis*: We expect the intervention to be superior compared to standard care in terms of reducing stress at the end of treatment (T1).

*Secondary hypotheses*: We expect the intervention to be superior to standard care in terms of improving health-related quality of life, functional capacity, self-efficacy, general distress, and stress at follow-up assessment time points (T2-T5). Furthermore, we expect the intervention to be superior to standard care in terms of reducing depression and anxiety symptoms, anger, and perceived stress. We expect the intervention to be superior compared to standard care in terms of cost-effectiveness.

*Other study goals* are to evaluate treatment satisfaction, usability, and perceived usefulness of the mHealth intervention. Furthermore, the study aims to evaluate predictors of usage behavior, time to dropout, and actual usage behavior. Actual usage behavior will be analyzed in terms of its influence on other study outcomes in an explorative approach.

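### The follow-up mixed ANOVA treats the pre-randomisation T0 value as a sixth outcome level, not as a covariate, so group differences at T2 to T5 are estimated less precisely than the collected data allow

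*Protocol article*

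**What the plan says.** The primary analysis is an ANCOVA of the combined stress measure at T1, with group as factor and the T0 value as covariate. For the later visits the Statistical methods section switches model: mixed ANOVAs with a group factor and "a within-subject factor for the respective measurement (T0-T5) will serve to assess if the effect of the intervention is maintained at follow-up". The Sample size calculation section describes the same model, a "mixed ANOVA with the respective measurements (T0–T5) as a within-subject factor", and names no covariate for it. The other endpoints get one sentence: "Further clinical endpoints will be analyzed in a similar fashion".

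The Study design section places T0 before randomisation. Table 1 schedules T0 for the stress measure and its components, quality of life, angina, walk test, blood pressure and self-efficacy. The imputation text counts baseline values of primary and secondary outcomes as complete. The Objectives section lists superiority on stress at T2 to T5 among the secondary hypotheses.

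**The concern.** Because T0 precedes randomisation, the expected group difference at T0 is zero. A mixed ANOVA with T0 as a response level does not use this. It estimates a free group difference at T0 and puts the treatment effect into the group-by-time interaction, where a T0-to-visit contrast is an unadjusted comparison of changes from baseline. Its group main effect averages the null T0 difference in with the post-baseline differences.

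At the plan's r = 0.5 a change score has the same variance as the raw outcome, so a contrast of this kind gains nothing from the baseline measurement. The ANCOVA used at T1 does gain from it. The secondary hypotheses at T2 to T5 would thus be tested with a less efficient model than the primary one, although the same baseline data are in hand, and a real follow-up effect is more likely to be missed.

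**Working it through.** **Inputs from the Sample size calculation section.** "We assume a moderate effect size of *d* = 0.5 for the baseline-adjusted comparison" at T1; "we expected the correlation between repeated measures to be" 0.5; 49 per group; "a preferred test power of 1-ß = 0.80 was chosen". The power stated for the mixed ANOVA assumes a group difference at T1 only.

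**Assumed here.** Two-sided alpha 0.05 (not stated), unit variance, the same correlation between all occasions, complete data, and d = 0.5 as a difference in raw SDs.

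**1. Reproduce the plan's ANCOVA figure.** Residual variance 1 − r² = 0.75. Standard error √(2 × 0.75/49) = 0.175. Noncentrality 0.5/0.175 = 2.86 on 95 df gives 80.8%, against the stated 80.34%. The inputs and the raw-SD reading of d therefore fit. If d were on the adjusted scale (raw difference 0.5 × √0.75 = 0.433), the same ANCOVA would have only 68.8%.

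**2. One follow-up visit, effect 0.5.**
- T0-to-visit contrast: variance 2(1 − r) = 1.0, standard error √(2/49) = 0.202, noncentrality 2.47 on 96 df: 68.8%.
- T0 as covariate: 80.8%, as in step 1.
- Loss: 12 points. The standard error is √(1/0.75) = 1.15 times as large. Simulation of the T1 comparison (20,000 trials) gave 68.8% and 80.5% to 80.9%.

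**3. Omnibus 5-df test, plan's T1-only pattern.**
- Group-by-time over T0 to T5: λ = n d² (5/6)/[2(1 − r)] = 49 × 0.25 × 0.833/1 = 10.2, F(5, 480): 68.2%.
- Joint group test over T1 to T5 adjusted for T0: covariance 0.5I + 0.25J, λ = 24.5 × 0.25 × 1.714 = 10.5: 69.6%.
- Loss: 1.4 points.

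**4. Effect of 0.5 held at all of T1 to T5 (an assumption, not the plan's pattern).**
- Joint 5-df test: λ = 10.2 again for group-by-time, 68.2%. Adjusted, λ = 24.5 × 0.25 × 5/1.75 = 17.5, about 92%.
- Mean of T1 to T5: the variance of the mean is (1 + 4r)/5 = 0.6. As a change from T0: 0.6 + 1 − 2(0.5) = 0.60, giving 88.6%. With T0 as covariate: 0.6 − 0.25 = 0.35, giving 98.5%.

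**5. Dependence on r (one visit, 49 per group).**

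| r | T0-to-visit contrast | T0 as covariate | Loss (points) |
|---|---|---|---|
| 0.4 | 60.9% | 76.2% | 15 |
| 0.5 | 68.8% | 80.8% | 12 |
| 0.6 | 78.2% | 86.5% | 8 |
| 0.7 | 88.6% | 92.9% | 4 |

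**6. Dependence on n (one visit, r = 0.5).** With 45 per group (64 × 0.7 = 44.8): 65.0% against 77.3%. With all 64 per group: 80.1% against 90.0%.

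**7. A contrast that does not gain.** For a later visit minus T1, Cov(Tk − T1, T0) = r − r = 0 under equal correlation, so T0 as covariate adds no precision.

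**The case against.** The case for leaving the plan alone is substantial. The mixed ANOVA is a legitimate secondary model: randomisation keeps it unbiased, and type I error is not inflated. The primary ANCOVA already adjusts for T0. The sample size section says the ANOVA serves to explore follow-up. All of this stands, and it limits the point to efficiency.

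Three stronger readings are tempting, and the document supports none of them.

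- *A loss of 12 to 23 points under the plan's own inputs.* The upper end needs d = 0.5 at every visit from T1 to T5. The article states only a T1 difference for this ANOVA, and the omnibus loss is then about 1 point. The 12-point figure belongs to a T0-to-visit contrast, which the article does not name.
- *A loss for every contrast.* Step 7 shows otherwise. A direct test of maintenance, comparing later visits with T1, gains nothing from the covariate under equal correlation.
- *All secondary endpoints go unadjusted.* "Further clinical endpoints will be analyzed in a similar fashion" follows a description of both the T1 ANCOVA and the mixed ANOVAs, so it may already include a baseline-adjusted T1 comparison. In addition, d and r are given only for the primary outcome, so figures for other endpoints are by analogy.

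Two replies do not remove the point. The stated 95.8% power for the mixed ANOVA offers no reassurance, because the plan's inputs give 68.2% at 49 per group; 98 per group gives 95.5%. Nor is the model an omitted detail left to an analysis plan: the article fixes T0 as a level of the time factor in two sections.

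**Conclusion.** The point holds as one of efficiency. Entering T0 as a response makes the estimated group differences at T2 to T5 less precise than the data allow. Validity is not in question, and the primary result is untouched.

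Under the stated assumptions, the loss for one visit is 12 points, which takes power from just above the plan's 0.80 target to below it. Across patterns, it runs from about 1 point (omnibus test, T1-only effect) through 10 (mean of T1 to T5, maintained effect) to 23 (joint test, maintained effect). It shrinks as the correlation rises. Secondary endpoints are affected only on one reading of the text, and by an amount that the document does not allow one to calculate. The change is worth making because it costs almost nothing, not because the planned model is wrong.

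**What to change.** In the Sample size calculation and Statistical methods sections, redefine the follow-up model:

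- Make T1 to T5 the repeated outcomes and drop T0 from the within-subject factor.
- Enter the T0 value of the same endpoint as a covariate, with its interaction with visit.
- Report the adjusted group difference at each of T2 to T5, and also at T1 for secondary endpoints.
- Say explicitly that the further clinical endpoints use this model, which removes the ambiguity.
- Restate the mixed ANOVA power figure for the new model, with its effect pattern, alpha and per-group n.

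This extends the primary ANCOVA to the later visits. It costs a wording change and one recalculated power figure. It needs no further data, visits or participants, since T0 is already scheduled for these endpoints.
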